### Inclusion Criteria

In order to be included in the present study, participants needed to be proficient in English, over the age of 18 years, currently pregnant, pregnant within the last year, or intending to become pregnant in the future. Interested women who met eligibility criteria were included in the present study regardless of depression status at study entry.

### Exclusion Criteria

Participants were excluded from participation in the present study if they were male, under the age of 18 years, not intending to become pregnant in the future, not pregnant, and not pregnant within the last year.

### Treatment Conditions

For the present trial, participants were randomly assigned to either the Internet-based CBT or CMT condition. The CBT condition, which did not have pregnancy-specific information within the course, included lessons on (1) thoughts, (2) activities, (3) assertiveness, and (4) sleep. [name] and the Institute for International Internet Interventions (i4health) team developed the materials for this condition, which is based on standard CBT constructs [23]. The CMT condition, which had a limited amount of pregnancy-specific content only in module three, included (1) finding ourselves here in the flow of life, (2) old brain, new brain, (3) the three circles of affect regulation and pregnancy, and (4) cultivating the compassionate self.

### Outcome Measures

Self-criticizing, self-attacking, and self-reassurance were assessed through the Forms of Self-Criticizing/Attacking and Self-Reassurance Scale (FSCRS; [24]). This measure identifies levels of self-criticizing and attacking and capacity for one to engage in self-reassurance [24]. In a sample of female college students, Cronbach alpha for inadequate self was at .90 and .86, for hated self and reassured self-subscales, respectively [24]. The FSCRS was administered to participants before and after the didactic portion of the course.

A Likert-scale affect item (“how would you rate your mood currently?” from 0-very bad to 7-very good) was employed to assess current affective state of participants at two time points during the course. The affect item was presented to participants at baseline and following the didactic portion of the course.

Depression and anxiety were assessed through the Patient Health Questionnaire-4 (PHQ-4; [25]. The PHQ-4 is a self-report measure that has two items to assess depression through the PHQ-2 and two items to assess anxiety through the Generalized Anxiety Disorder scale-2 (GAD-2) [26]. Based on a sample from the general population, Cronbach alpha was .78 for PHQ-2 and .75 for GAD-2 [25]. When compared to the Structured Clinical Interview for DSM-IV Disorders (SCID-4), a scaled score of 3 on the PHQ-2 scale demonstrated sensitivity of 87% and specificity of 78% for Major Depressive Disorder (MDD), and it demonstrated comparable diagnostic performance relative to longer measures [27]. The PHQ-4 was administered before the didactic portion of the course and following completion of post course measures at two weeks.

Self-compassion shifts were measured through the short form of the Self-Compassion Scale (SCS-SF; [28]). The SCS-SF measures how individuals respond to themselves during times of stress in order to assess level of self-compassion [28]. The SCS-SF has a near perfect correlation with the longer version of the measure at .97. It has a Cronbach alpha of .86 in the general population in the United States [28]. The SCS-SF was given to participants before the didactic portion of the course and after completion of post course measures at two weeks*.*

Participant feedback items were asked at post course to elicit information on use (ie, the number of times materials were practiced during each week, overall perceived helpfulness of the materials). While no formalized measure was given to elicit feedback, the information on perceived helpfulness and utilization was gathered in order to provide participant-directed guidance for updating the CMT condition materials.

For a visual representation of the study design, refer to Figure 1.

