**Results:**

Post course data was gathered at two weeks. A 2x2 repeated measures analysis of variance will be conducted to analyze differences between conditions at post course.

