The present study therefore seeks to assess the efficacy of an Internet-based Compassionate Mind Training (CMT) program, the intervention component of CFT, compared to a standard CBT program in a sample of childbearing and perinatal women. As there is currently a lack of Internet interventions for maternal mental health, the research team intends to assess the relative efficacy of CMT as a resource for women during this period.

It is expected that participants randomized to both Internet-based CMT and CBT will demonstrate improved affect as well as reduced depression and anxiety at similar, if not better, levels which are the secondary outcome measures of this trial. However, in terms of the primary outcome measures, we expect that Internet-based CMT will provide unique benefit above and beyond CBT in the constructs of self-reassurance, self-criticizing, self-attacking, and self-compassion, as CMT is specifically targeted towards these constructs.

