### Analysis

The present study seeks to compare the efficacy of two theoretical approaches using a randomized conditional approach with outcome comparisons at baseline, throughout the course period, and at the post course two weeks following randomization. Pre course equivalence between participants in each condition will follow analytical procedures recommended by the CONSORT 2010 Statement [29]. A 2x2 mixed analysis of variance (ANOVA) will be run for each measure at baseline and follow-up. The between subjects factor in the ANOVA will be condition and the within subjects factor will be the outcome measure. A main effect of time and a main effect of condition will be analyzed to determine if there is a difference between CBT and CMT on each of the outcome measures.

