MTurk workers received compensation when they completed post course data at two weeks. There is an inherent limitation with a highly motivated sample of women who will receive compensation for completing post course data in order to receive payment for their participation. Internet-based research has a high level of attrition [35], and thus the completion rates witnessed with an MTurk sample are unlikely to be generalizable to a broader group of international perinatal women. As such, it is impossible to know what actual attrition rates would be in a non-MTurk group of women if the majority of recruitments comes from this source.

Perhaps the most important and glaring limitation of the current trial is the lack of a more distal time point for measurement of outcome variables. The limited follow-up with participants, only occurring at two weeks post course, does not allow the team to make inferences about the longer-term maintenance of improvements in either condition. As the ultimate goal of psychological Internet interventions is to decrease suffering on a global scale, knowledge of longer-term utility of these resources is crucial. In order to account for this limitation during future research along this same line, we will add another follow-up after pregnancy, which can be up to six months after providing baseline data.

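### Three of the four primary constructs (FSCRS) have no stated two-week measurement, although the abstract and sample size tie the comparison to the two-week post course

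*Protocol article*

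**What the plan says.** The Introduction sets the primary hypothesis: "Internet-based CMT will provide unique benefit above and beyond CBT in the constructs of self-reassurance, self-criticizing, self-attacking, and self-compassion". Affect, depression and anxiety are named there as secondary.

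Outcome Measures assigns an instrument and a schedule to each:

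- "Self-criticizing, self-attacking, and self-reassurance were assessed through the Forms of Self-Criticizing/Attacking and Self-Reassurance Scale", and "The FSCRS was administered to participants before and after the didactic portion of the course".
- The affect item is likewise given at baseline and after the didactic.
- For self-compassion, "The SCS-SF was given to participants before the didactic portion of the course and after completion of post course measures at two weeks". The PHQ-4 (depression and anxiety) has the same two times.

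Participants and Procedures splits each condition into two equal parts. Part (a) is the didactic, built to last about 45 minutes. Once it is finished, women are emailed the part (b) material: follow-up exercises for CBT and audio meditations for CMT. The same section requires at least 23 women per condition who complete the two-week assessment, and sets recruitment at 60 per condition.

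The abstract states "Post course data was gathered at two weeks" and plans a 2x2 repeated measures ANOVA of differences between conditions at post course. The Analysis section plans a 2x2 ANOVA for each measure at baseline and follow-up. It lists comparisons at baseline, during the course, and "at the post course two weeks following randomization". The limitations in the Discussion speak of "The limited follow-up with participants, only occurring at two weeks post course".

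**The concern.** The primary hypothesis credits CMT as a programme with benefit beyond CBT. For three of its four constructs, the only post-baseline measurement the text describes comes after the didactic and not at the end of the course. A difference on the FSCRS would then reflect part (a) alone. A reader of the abstract would take it as a result of the two-week course, including the practice period that has not started when the scale is completed.

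The limitations paragraph adds to this. It presents the absence of follow-up beyond two weeks as the main weakness, without saying that most primary constructs are not stated to be followed even that far. The sample size is also counted at an assessment where, on the stated schedule, these constructs are not measured. It therefore does not identify the women who contribute to the FSCRS comparison.

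**Working it through.** The point is settled by setting the stated schedule against the stated comparison.

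| Construct | Status | Instrument | Before didactic | After didactic | Two weeks |
|---|---|---|---|---|---|
| Self-reassurance | primary | FSCRS | yes | yes | not stated |
| Self-criticizing | primary | FSCRS | yes | yes | not stated |
| Self-attacking | primary | FSCRS | yes | yes | not stated |
| Self-compassion | primary | SCS-SF | yes | not stated | yes |
| Affect | secondary | single item | yes | yes | not stated |
| Depression | secondary | PHQ-4 | yes | not stated | yes |
| Anxiety | secondary | PHQ-4 | yes | not stated | yes |

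Status is from the Introduction; instruments and times are from Outcome Measures.

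1. Count without a stated two-week value: 3 of 4 primary and 1 of 3 secondary, so 3 + 1 = 4 of 4 + 3 = 7 outcomes.
2. Each measure has two stated times, so a 2x2 ANOVA (condition by time) can be formed for all seven. The second time is post-didactic for four of them and two weeks for three.
3. The abstract gives one comparison, at post course, and one time for post-course data, two weeks. Only the three outcomes from the SCS-SF and PHQ-4 fit that description.
4. The Analysis section is looser. Its reference to comparisons during the course can cover a post-didactic FSCRS analysis, and follow-up can mean each measure's own second time. It does not say which measure belongs to which time.
5. Order of events: the part (b) material is emailed after part (a) is completed. If the second FSCRS is taken at the end of part (a), no part (b) exposure precedes it.
6. Definition of the two-week point: the Analysis section counts from randomisation, the Discussion from the course. If the course fills 14 days from randomisation, the literal Discussion reading is day 14 + 14 = 28, against day 14 in the Analysis section.

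The plan's one figure here is 23 completers per condition (effect 0.4, alpha 0.05, 80% power). It can be neither confirmed nor refuted, because the sidedness, the within-person correlation and the precise effect being tested are not given. A plain two-sided two-group difference of 0.4 SD needs 2 × (1.960 + 0.842)² / 0.4² = 98.1, so 99 per arm. A group-by-time interaction with f = 0.2 needs 26 per arm at correlation 0.5 and 21 at 0.6. The present point does not depend on this. What matters is only that the 23 are counted at two weeks.

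**The case against.** The strongest reply is that the absence of a two-week FSCRS is inferred. The text does not say the scale was given only twice, and it mentions other post-course measures at two weeks without listing them all. The study design is in Figure 1, which is not shown. This stands as a limit on certainty. Still, the article gives a separate schedule for each instrument and names two weeks for two of them, and the only other post-course items it describes are feedback questions. If the figure does show a two-week FSCRS, the text needs correcting to match it.

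Second, the Analysis section permits a comparison during the course. This also stands: the FSCRS can be analysed, and the defect is the missing link between measure and time point.

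Third, a sample counted at the later assessment is normally a safe floor for an earlier one. That is fair. The mismatch does not by itself mean too few women for the FSCRS.

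Fourth, the article calls the trial a pilot and disclaims decisive conclusions about treatment effectiveness. That tempers the consequence, but the directional primary hypothesis about the programme remains.

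A reader might infer more than the documents support:

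- That the FSCRS reflects a single lesson. Treatment Conditions lists four modules per condition, and the didactic is one of two equal parts of the course.
- That demand effects favour CMT. Nothing in the article shows this, and the targeting argument would apply equally to the SCS-SF.
- That many women with valid FSCRS data will be dropped. No restriction of the FSCRS analysis to two-week completers is stated.

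**Conclusion.** The point holds as a contradiction in the stated text. Three of four primary constructs, and the secondary affect item, have no stated two-week measurement, while the abstract describes the between-condition comparison at the two-week post course and the sample size counts completers there. A post-didactic FSCRS comparison is feasible and falls within the Analysis section. It can support a claim about part (a), but not about the full two-week course. Of the four primary constructs, only self-compassion can bear a two-week claim.

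This rests on two assumptions: that Figure 1 adds no further FSCRS administration, and that the second FSCRS was taken at the end of part (a), before the part (b) material was used. A reader might conclude that the FSCRS constructs should lose primary status. The documents do not require that. Recruitment closed in September 2015 and the abstract reports two-week data as gathered, so demoting three pre-specified primary outcomes now would be a debatable endpoint change. Defining their time point resolves the conflict.

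**What to change.** Reconcile the abstract, Participants and Procedures, Outcome Measures, Analysis and the limitations in the Discussion, before outcomes are compared by condition:

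1. Name the time point of the comparison for each measure. If a two-week FSCRS administration exists, state it in Outcome Measures.
2. If it does not, keep the three FSCRS constructs primary and define them as post-didactic outcomes. Analyse them, and the affect item, in all randomised women with a post-didactic value and not only in two-week completers.
3. Limit the interpretation of FSCRS and affect results to part (a). Let claims about the two-week course rest on the SCS-SF (primary) and the PHQ-4 (secondary).
4. State that the count of 23 completers per condition refers to the measures taken at two weeks.
5. Add to the limitations that the FSCRS constructs and affect were not followed beyond the didactic.
6. Give one definition of the two-week assessment, from randomisation or from the end of the course.

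The cost is a narrower FSCRS claim and some rewording. No new data are needed and no outcome changes rank.

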**Figure 1 figure1:**
[figure not shown]
Design of the study.

### Ethics

The present study received approval by the Palo Alto University Institutional Review Board and is being conducted under the supervision of [name].

### Analysis

The present study seeks to compare the efficacy of two theoretical approaches using a randomized conditional approach with outcome comparisons at baseline, throughout the course period, and at the post course two weeks following randomization. Pre course equivalence between participants in each condition will follow analytical procedures recommended by the CONSORT 2010 Statement [29]. A 2x2 mixed analysis of variance (ANOVA) will be run for each measure at baseline and follow-up. The between subjects factor in the ANOVA will be condition and the within subjects factor will be the outcome measure. A main effect of time and a main effect of condition will be analyzed to determine if there is a difference between CBT and CMT on each of the outcome measures.

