## Methods

### Participants and Procedures

Participants were recruited through two primary sources: online through Amazon Mechanical Turk (MTurk) and through professional networks. Recruitment for the present study occurred between April 2015 to September 2015.

Upon navigating to the landing page, participants were asked to review and agree to informed consent (IC) before beginning the study. For a copy of the IC for the present study, see Multimedia Appendix 1. Participants who met criteria for inclusion were then randomized to either the CBT (n=60) or CMT (n=60) condition. As the trial was designed to assess the efficacy among perinatal women of an Internet-based CMT relative to an Internet-based CBT intervention, a control group was not employed. To ensure equivalent numbers of participants were randomized to both conditions, an embedded algorithm was used.

Each condition was divided into equal parts (a) and (b) with condition-specific content reflective of the theoretical orientation of the intervention. In part (a), participants completed a didactic, which included written materials and brief experiential exercises. The didactic portion of the course provided an introduction to the approach and was created to take approximately 45 minutes to complete. Following completion of part (a), participants received an automatically generated email based on their assigned condition. The email included follow-up exercises for the CBT condition and audio meditations for the CMT condition. At this point, participants were informed that they would receive additional emails at Day 4, Day 7, and Day 14 of the course.

Based on a power analysis to detect an effect of .4 at alpha .05 with 80% power, this study needed to include a minimum of 23 participants for each condition who complete the post course assessment at two weeks. The standardized effect size was estimated using [21] and the meaning of this size is .25 for small, .5 for medium and 1.00 for large. The designated medium effect size is consistent with what is universally agreed upon in published mindfulness research [22]. However, the research team tried to recruit 60 participants for each condition in order to account for attrition that is inherent in clinical trial, especially ones conducted over the Internet.

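### The named ANOVA contrast for comparing the arms averages in baseline; modelling follow-up on condition and baseline score targets the right difference with more precision

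*Protocol article*

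**What the plan says.** The Analysis section of the protocol article fixes the model: "A 2x2 mixed analysis of variance (ANOVA) will be run for each measure at baseline and follow-up". It describes the factors by saying that condition is between subjects and that "the within subjects factor will be the outcome measure"; a 2x2 layout at two occasions needs time in that place. It then names the tests: "A main effect of time and a main effect of condition will be analyzed to determine if there is a difference between CBT and CMT". It names neither the condition-by-time interaction nor a model that adjusts follow-up for baseline. The Abstract (Results) also plans a 2x2 repeated measures ANOVA and gives its purpose as the difference between conditions at post course.

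The Outcome Measures section shows that the FSCRS, SCS-SF, PHQ-4 and affect item are each taken before the didactic and once more later. The later occasion is two weeks for the SCS-SF and PHQ-4, and directly after the didactic for the FSCRS and affect item.

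Participants and Procedures gives the sample size reasoning: "Based on a power analysis to detect an effect of .4 at alpha .05 with 80% power", leading to "a minimum of 23 participants for each condition who complete the post course assessment at two weeks", with 60 randomised per arm. No pre-post correlation or SD is given.

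**The concern.** There are two problems, one inside the other.

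First, the contrast named for the arm comparison is the main effect of condition. In a pre/post ANOVA this compares the arms on the average of baseline and follow-up. Randomisation makes the expected baseline difference zero, so the average carries only half of any follow-up difference, and chance baseline imbalance enters it directly.

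Second, even if the interaction is tested instead, a two-occasion ANOVA reduces to a comparison of change scores. That forces the slope of follow-up on baseline to be 1. Estimating the slope uses the same data and gives a more precise estimate of the same difference.

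At stake is the chance of detecting the benefit over CBT that the Introduction expects from CMT on the primary outcomes. Recruitment has ended, so sample size can no longer be changed, and the analysis is where precision can still be gained.

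**Working it through.** **The plan's own figure.** The only related figure is 23 completers per arm. Reading 0.4 as a standardised mean difference, two-sided alpha .05 and 80% power:

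n = 2(1.96 + 0.8416)² / 0.4² = 98.1, so 99 per arm (78 one-sided).

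This does not reproduce 23. Other readings come close. If 0.4 is Cohen's f (a mean difference of 0.8 SD), the same formula gives 25 per arm, and the exact t test 26. A repeated-measures between-factor F test with f = 0.4 gives 22 to 24 at r of .7 to .8. A change-score test with a difference of 0.4 SD gives 23 only at r = 1 - 23/(2 × 99) = .88. The article does not say which applies; its benchmarks ("the meaning of this size is .25 for small, .5 for medium and 1.00 for large") do not settle the metric.

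**Inputs for the comparison of methods.** From the article: two occasions per measure, 1:1 randomisation, 60 per arm, effect 0.4, alpha .05. Assumed: 0.4 is a difference in SD units at follow-up, the test is two-sided, SDs are equal at both occasions and in both arms, all 60 per arm give follow-up, and r takes values from .3 to .9.

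**Formulas.** Variance of each estimate of the follow-up difference, in units of 2σ²/n:

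- Condition-by-time test (change score): 2(1-r)
- Follow-up adjusted for baseline (ANCOVA): 1-r²
- Main effect of condition, doubled so that it estimates the follow-up difference: 2(1+r)

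ANCOVA divided by change score is (1+r)/2, a cut of (1-r)/2. ANCOVA divided by the main effect is (1-r)/2, a cut of (1+r)/2. Power is Φ(0.4/√(2v/n) - 1.96), where v is the variance factor.

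| r | v, change | v, ANCOVA | v, main effect | Cut vs change | Cut vs main effect | Power at 60 per arm: change / ANCOVA / main effect |
|---|---|---|---|---|---|---|
| .3 | 1.40 | 0.91 | 2.60 | 35% | 65% | 46% / 63% / 27% |
| .5 | 1.00 | 0.75 | 3.00 | 25% | 75% | 59% / 72% / 24% |
| .7 | 0.60 | 0.51 | 3.40 | 15% | 85% | 81% / 87% / 22% |
| .9 | 0.20 | 0.19 | 3.80 | 5% | 95% | above 99% / above 99% / 20% |

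Worked example at r = .5, main effect: √(2 × 3.00/60) = 0.316; 0.4/0.316 = 1.265; Φ(1.265 - 1.96) = 24%.

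**Small samples.** The slope must be estimated, which costs a little. A simulation of 20,000 trials with 23 per arm gave a cut against the change score of 22% at r = .5 (formula 25%) and 13% at r = .7 (formula 15%). All three methods were unbiased for the follow-up difference once the main effect was doubled.

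**Power at 23 per arm**, same assumptions, change / ANCOVA / main effect: 27% / 35% / 12% at r = .5 and 42% / 48% / 11% at r = .7.

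**The case against.** The strongest reply is that a change-score comparison is unbiased and valid under randomisation, so that once the interaction is tested the choice is one of efficiency, and covariate adjustment is often settled in a full analysis plan. The first part stands: against the interaction this is an improvement, not the repair of an error. The second part does not remove the point, because the article itself fixes the model and the effects to be tested, and the effect it names for the arms is not the interaction.

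A second reply is that the gain may be small. The FSCRS is repeated after a didactic of about 45 minutes, and r could be high over so short an interval; at r of .8 to .9 the cut against the change score is only 10% to 5%. That also stands, and it is why no single percentage can be given. A high r does not help the named main effect, whose variance grows with r.

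A reader might infer that the trial is plainly far below its stated power at 23 per arm. The documents do not support that without a condition. It follows if 0.4 is a standardised mean difference and r is moderate; it does not follow if 0.4 is Cohen's f or if r is near .88. The 23 also counts two-week completers, which is not the sample for the FSCRS or the affect item. Nor would baseline adjustment justify 23: for a difference of 0.4 SD it would still need 74 per arm at r = .5 or 51 at r = .7.

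A reader might also want recruitment source (MTurk or professional networks) in the model. The article describes no stratification by source, and nothing in it supports adding that term.

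**Conclusion.** The point holds. Taken literally, the Analysis section tests the arms with a contrast that estimates half the follow-up difference, at about 24% power for 0.4 SD with 60 per arm and r = .5. Read generously as the condition-by-time test, the plan is valid but less precise than baseline adjustment at every r below 1. The loss is (1-r)/2 of the variance: 35% at r = .3, 25% at .5, 15% at .7, 5% at .9, and slightly less at small n.

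The direction against the change score rests on randomisation and equal SDs; the size rests on r, which the article does not give. A cut of 15% to 25% is therefore what r of .7 to .5 would imply, and not an established property of this trial. The power figures further assume that 0.4 is a standardised mean difference and that all 60 per arm give follow-up.

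**What to change.** For each outcome, make the main arm comparison a linear model of the follow-up score on condition and the baseline score of the same measure. Report the adjusted difference between arms with its 95% CI. Keep the 2x2 ANOVA as a supportive display, with time stated as the within-subjects factor and the condition-by-time term as the one that bears on differential change.

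No new data are needed. The statistical cost is one degree of freedom and the small loss from estimating the slope. The procedural cost is real: recruitment is closed and the Abstract reports two-week data as already gathered, so the change must be dated, justified and recorded before outcomes are examined by arm.

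### The plan judges CMT against CBT by the main effects of time and condition and never names the condition-by-time contrast that measures the difference

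*Protocol article*

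**What the plan says.** The Analysis section of the protocol article sets out the model as follows: "A 2x2 mixed analysis of variance (ANOVA) will be run for each measure at baseline and follow-up". It defines the factors in the next sentence: "The between subjects factor in the ANOVA will be condition and the within subjects factor will be the outcome measure". It then says which terms answer the trial's question: "A main effect of time and a main effect of condition will be analyzed to determine if there is a difference". The sentence goes on to make clear that the difference meant is the one separating the two courses, judged outcome by outcome.

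The Results paragraph of the abstract describes the same model with a slightly different target: "A 2x2 repeated measures analysis of variance will be conducted to analyze differences between conditions at post course".

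The Introduction gives the hypotheses these tests must serve. The primary one is a superiority claim: "we expect that Internet-based CMT will provide unique benefit above and beyond CBT in the constructs of self-reassurance, self-criticizing, self-attacking, and self-compassion". For the secondary outcomes, improvement is expected in both arms: "participants randomized to both Internet-based CMT and CBT will demonstrate improved affect as well as reduced depression and anxiety".

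The article nowhere mentions a condition-by-time interaction, a between-arm comparison of change, or a comparison at follow-up adjusted for baseline.

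**The concern.** With two arms and two assessments, the model has three terms, and only the interaction isolates what the randomised treatments did differently. The plan names the other two as deciding terms.

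- **Time** compares follow-up with baseline over both arms together. It is non-zero whenever participants improve, drift or regress to the mean, even if the two courses are equally good. The Introduction expects improvement in both arms on affect, depression and anxiety, so a significant time effect is anticipated there even if the arms do not differ.
- **Condition** compares the arms on the mean of baseline and follow-up. The baseline precedes the intervention, so in expectation it contributes no treatment effect. It dilutes the follow-up difference and adds half of any chance imbalance at baseline.

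The factor definition is also wrong. The within-subject factor is given as the outcome measure, although the ANOVA is run separately for each measure and an effect of time is to be tested. The factor has to be time.

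The same sentence governs every outcome, so the primary conclusion on self-reassurance, self-criticizing, self-attacking and self-compassion depends on it.

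**Working it through.** **Inputs from the article** (Methods, Participants and Procedures): effect size 0.4; alpha .05 (taken here as two-sided); 60 randomised per arm; a stated minimum of 23 completers per arm. The article gives no power figure for any ANOVA term, so there is none to reproduce. The arm sizes are used as given.

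**Assumptions, not in the article:** SD 1 at both assessments; pre-post correlation r, shown from 0.3 to 0.8; 0.4 read as a standardised difference d at follow-up; equal baseline means in expectation by randomisation, with no differential loss; for the time effect, a common improvement of 0.3 SD in both arms.

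**Step 1. What each term estimates.** The expected arm difference is 0 at baseline and d at follow-up.

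- Condition: (0 + d)/2 = d/2, which is 0.20 when d = 0.4. This does not depend on r.
- Condition-by-time: d − 0 = d, which is 0.40.
- Time: the average change over both arms, with no between-arm contrast.

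**Step 2. Standard deviations.** The pre-post mean has SD √((1+r)/2). The change has SD √(2(1−r)).

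**Step 3. Noncentrality** for n per arm is effect / (SD × √(2/n)). With r = 0.6 and n = 60, √(2/60) = 0.1826.

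- Condition: 0.20 / (0.8944 × 0.1826) = 1.22, power 23%.
- Condition-by-time: 0.40 / (0.8944 × 0.1826) = 2.45, power 68%.

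Both SDs equal √0.8 = 0.8944 at this r, so the gap here comes wholly from the halved effect. In general the ratio of the two noncentralities is √((1+r)/(1−r)), which exceeds 1 for every r above 0.

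**Step 4. Power over the range of r** (noncentral t, d = 0.4). The last two columns show a baseline-adjusted comparison (ANCOVA, residual SD √(1−r²)) for reference.

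| r | Condition, 60/arm | Condition-by-time, 60/arm | Condition, 23/arm | Condition-by-time, 23/arm | ANCOVA, 60/arm | ANCOVA, 23/arm |
|---|---|---|---|---|---|---|
| 0.3 | 27% | 45% | 13% | 20% | 62% | 29% |
| 0.5 | 24% | 58% | 12% | 26% | 71% | 33% |
| 0.6 | 23% | 68% | 12% | 32% | 78% | 38% |
| 0.7 | 22% | 80% | 11% | 40% | 86% | 46% |
| 0.8 | 21% | 93% | 11% | 55% | 95% | 60% |

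Simulation gave mean estimates of about 0.20 for the condition effect and 0.40 for the interaction, with matching rejection rates. With no arm difference, the condition effect rejected in about 5% of runs.

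**Step 5. The time effect when the arms do not differ.** Noncentrality is 0.3 / √(2(1−r)/(2n)). With r = 0.6:

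- n = 23: 0.3 / √(0.8/46) = 2.27, significant in about 60% of trials.
- n = 60: 0.3 / √(0.8/120) = 3.67, significant in about 95% of trials.

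With a common improvement of 0.5 SD and r from 0.5 to 0.8, simulation gave 91% to 99.9% at 23 per arm and over 99.9% at 60 per arm.

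**The case against.** The strongest reply has five parts.

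1. *The condition main effect is a valid test.* This stands. Under randomisation it keeps its 5% type I error, and a significant result is evidence that the arms differ. Its faults are a halved estimate and low power. The risk of a false conclusion comes from the time effect.

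2. *The time effect is meant for the hypothesis that both arms improve, and the sentence merely merges two aims.* That is a plausible account of how the sentence arose. As written, though, it assigns both terms to the between-arm question and gives that question no other test.

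3. *A 2x2 mixed ANOVA contains the interaction, and an analysis plan may designate it.* The model does contain it. But the article is not silent on the deciding terms: it names them, and names the wrong ones. A choice made once the output is visible is no longer prespecified.

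4. *The power figures rest on an assumed correlation, and low power at 23 per arm is largely sample size.* Both points are fair. The gap narrows as r falls, and the interaction itself reaches only 20% to 55% at 23 per arm over the range shown. The halving and the direction of the gap (for r above 0) do not depend on the value assumed.

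5. *The interaction is not the most efficient choice.* Correct: ANCOVA has more power, and a change score remains sensitive to chance baseline imbalance when r is below 1. This widens the choice of remedy and does not defend the main effects.

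The Discussion calls the study preliminary and disclaims decisive conclusions on treatment effectiveness. That limits the harm, but relative efficacy remains the stated aim and superiority the primary hypothesis.

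**Conclusion.** The concern holds. The Analysis section designates two terms that do not measure the difference between CMT and CBT and omits the one that does. The condition effect recovers half of the true follow-up difference, a result that needs only randomisation and no differential loss. The time effect carries no information on which arm did better.

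For d = 0.4, 60 per arm and r between 0.3 and 0.8, acting on the condition effect leaves power at 21% to 27%, against 45% to 93% for the difference in change. Reading a significant time effect as a difference between arms would be wrong in most trials where both arms improve equally by 0.3 SD, given r = 0.6. The correlation and the common improvement are assumptions. The mislabelled within-subject factor is a lesser fault, since the rest of the paragraph shows that time is meant, but it should be corrected with the rest. The error affects the deciding test for every outcome and must be corrected before the data are analysed.

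**What to change.** Replace the last two sentences of the Analysis section with wording such as:

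> The between-subject factor is condition and the within-subject factor is time (baseline, follow-up). For each outcome, CMT is compared with CBT by the condition-by-time interaction, reported as the between-arm difference in change with its 95% confidence interval. The main effects of time and condition are descriptive and are not used to conclude that the conditions differ.

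A comparison of follow-up scores adjusted for baseline would serve equally well. It has more power and fits the abstract's aim of comparing conditions at post course. One of the two should be chosen and fixed before the outcome data are examined.

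The text should also name the second assessment for each outcome. Under Outcome Measures, the FSCRS and the affect item are repeated after the didactic, while the PHQ-4 and SCS-SF are repeated at two weeks. The abstract should be brought into line.

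The cost is a change of wording. The data, sample size and software stay the same.
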